## Background

SABR is emerging as a non-invasive method for precision irradiation of pulmonary oligometastases using radioablative doses with a higher biological effect than can be achieved with conventional radiotherapy. The paradigm of aggressive local treatment with SABR for oligometastatic disease is well recognised [1–3]. Stereotactic body ‘radiosurgery’ (SRS) refers to the accurate delivery of a single precise, large and highly conformal SABR treatment. Multi-fraction SABR and single fraction SABR represent a radical departure from classical fractionated radiotherapy. A previous systematic review [4] of SABR for secondary lung cancers performed in 2010 revealed 154 patients treated with single fraction SABR and 343 patients treated with fractionated SABR. In the single fraction experience, the mean weighted 2 year local control was 78.6 % (range 48–91 %) and 2 year overall survival was 50.3 % (range, 33–73 %). The rate of significant toxicity (grade 3 or higher) was only 3.3 %. The results are comparable in the fractionated SABR series. The 2-year weighted local control was 77.9 % (range, 67–96 %). The corresponding 2-year weighted overall survival was 53.7 % (range 33–89 %), with a 4 % rate of grade 3 or higher radiation toxicities. These outcomes are comparable with surgical alternatives, with low rates of significant toxicity.

Stereotactic radiotherapy is a rapidly evolving technique that has been implemented widely through Europe, North America and Japan. A survey of 1600 American radiation oncologists showed that 64 % of physicians used SABR (95 % confidence interval, 60–68 %), of whom nearly half adopted it in 2008 or later [5]. Lung was the most popular site of SABR use (89 %), with the three and four fraction SABR schemes accounting for 68 % of prescribed treatments. In contradistinction the single fraction approach is commonly employed by several institutions in Europe [6–10]. Similarly in the Australian context several dose-fractionation schedules have been developed. For example the Peter MacCallum Cancer Centre in Victoria has reported the use of a single fraction technique [11], whereas the Northern Sydney Cancer Centre have implemented a four fraction SABR approach in New South Wales. A retrospective comparison of these two approaches indicated no significant differences in clinical outcomes between single or multi-fraction approaches [12].

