**Fig. 1 Fig1:**
[figure not shown]
Study flowchart

**Table 2 Tab2:** Normal tissue dose-volume constraints and standardised contouring nomenclature

Organ	Standardised name	Parameter	Investigational treatment	
		Constraint	28Gy in 1#	48Gy in 4#/2wks
Normal Lungs		V5 < 1000 cc	66 % 7.4Gy	66 % 12.4Gy, (max 3.1Gy per fraction)
Heart	Heart	Maximum dose (0.03 cc) < 15 cc	22Gy	34 Gy, (max 8.5 Gy per fraction)
			16Gy	28 Gy, (max 7 Gy per fraction)
Oesophagus	Oesophagus	Maximum dose (0.03 cc)	15.4Gy	30Gy, (max 7.5Gy per fraction)
Spinal Cord	SpinalCord	Maximum dose (0.03 cc)	12Gy	20.8Gy, (max 5.2Gy per fraction)
Brachial plexus	BrachialPlexus	Maximum dose (0.03 cc)	15Gy	24Gy, (max 6Gy per fraction)
Skin (5 mm subcutis)	Skin	Maximum dose (0.03 cc) < 10 cc	26Gy	36 Gy, (max 9 Gy per fraction)
			23Gy	33.2 Gy, (max 8.3 Gy per fraction)
Chest wall^a^	ChestWall	<70 cc	^b^26Gy to full thickness	30Gy
Great Vessels	GreatVessel	Maximum Dose (0.03 cc)	30 Gy	49 Gy, (max 12.25 Gy per fraction
Liver	Liver	V20, V30	No constraint, but dose/volume parameters to be documented	No constraint, but dose/volume parameters to be documented

^a^Chest wall dose limit may be exceeded if rib structure lies close to or in contact with the PTV

^b^26Gy isodose line should not cross full thickness of the chest wall structure

Definitions: Vx describes the volume that receives xGy, e.g. V5 < 66 % represents that the volume of specified OAR receiving 5 Gy shall be less than 66 %

The primary endpoint is safety of SABR treatment as measured by the incidence of grade 3 and 4 toxicities measured using CTCAE V4.0 within 12 months of treatment completion. Key secondary endpoints include a) Quality of life using EQ-5D and MDASI-LC, b) Local efficacy (time to local failure), c) Resource use and costs associated with treatment, d) Other clinical outcomes (overall survival, time to distant failure and disease free survival).

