### Statistical considerations

This study is a randomised controlled phase II multicentre trial, with the main objective to determine whether single fraction radiosurgery (28Gy/1) or fractionated SABR (48Gy/4) has acceptable toxicity for the treatment of pulmonary oligometastases, as defined by a maximum acceptable toxicity rate of grade 3 or higher adverse events of < 5 %.)

If both treatments have acceptable toxicity profile the criteria for selecting which arm will be used in the phase III trial is as follows:The arm with superior clinical outcomes will be chosen, based on time to local failure and overall survival.If there is no significant difference in clinical outcomes, the arm with the superior quality of life will be chosen.If there is no significant difference in quality of life, the arm associated with the least amount of resource use will be chosen.

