### Statistical analysis

Toxicities will be summarised as counts and percentages and presented in tabular form. The rate of grade 3 or higher toxicities at 1 year will be estimated for each arm by two methods. The first method (primary analysis) will evaluate the toxicities for participants who complete 1 year of follow up with 80 % confidence interval assuming binomial distribution. The second method (sensitivity analysis) will estimate the toxicities using cumulative incidences with death as a competing event. Time to event outcomes will be described using Kaplan-Meier methods with 95 % confidence intervals for each arm. The curves will be compared between arms using the Logrank test.

Overall Health-Related Quality of Life (HRQOL) will be measured using the MDASI-LC, a 22 item QoL module with three specific lung cancer questions. The results will be analysed using general linear mixed models. The area under the curve (AUC) will be compared between the arms using linear contrasts from the general linear mixed model. The linear mixed model will include arm, time and the interaction between arm and time as fixed effects with patients as random effect. Baseline MDASI-LC will be included as a covariate in the model. Completion rate of MDASI-LC at each time point will be reported in tabular form.

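### Kaplan-Meier description of time to local and distant failure censors deaths and overstates the proportion of patients who fail; cumulative incidence should be reported instead

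*Protocol article*

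**What the plan says.** In the protocol article, the endpoint paragraph after Table 2 (Study design) lists "Local efficacy (time to local failure") as one key secondary endpoint and, separately, "Other clinical outcomes (overall survival, time to distant failure and disease free survival"). The Statistical analysis section then treats all time-to-event outcomes alike: "Time to event outcomes will be described using Kaplan-Meier methods with 95 % confidence intervals for each arm", and "The curves will be compared between arms using the Logrank test". No exception is made for the two failure endpoints.

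In the same paragraph the plan handles death differently for toxicity: "The second method (sensitivity analysis) will estimate the toxicities using cumulative incidences with death as a competing event".

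Under Statistical considerations, local failure helps to decide which arm goes to phase III, provided both arms have acceptable toxicity: "The arm with superior clinical outcomes will be chosen, based on time to local failure and overall survival". Follow-up runs to year 5 (Study design).

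**The concern.** A patient who dies without local failure can no longer have one. Kaplan-Meier treats that patient as censored, that is, as still able to fail at the same rate as those alive. So 1-KM estimates failure in a setting where nobody dies first. It does not estimate the share of treated patients whose lesions recur, which is how a published failure percentage is usually read.

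The Background cites a review in which roughly half the patients had died by 2 years, so the two quantities could differ visibly. The plan accepts the principle for a 1-year toxicity endpoint but does not carry it to endpoints followed for up to 5 years, when more patients will have died. At stake are the reported local and distant failure percentages and their confidence intervals, which a reader might carry into counselling or into the design of the phase III trial.

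**Working it through.** **What the plan offers to check.** The article states no expected failure rate, event number or power for local or distant failure. Its sample size (38 evaluable per arm; 38/0.92 = 41.3, rounded up to 42) concerns toxicity and does not bear on this point. The check therefore uses the figures cited in the Background.

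**Inputs**
- Single fraction: "the mean weighted 2 year local control was 78.6 % (range 48–91 %) and 2 year overall survival was 50.3 % (range, 33–73" %).
- Multi-fraction (Background, same review): 2-year local control 77.9 %, 2-year overall survival 53.7 % (range 33 to 89 %).
- Local control of about 90 % at these dose levels (Background, text with Table 1).

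Deaths by 2 years are thus 100 − 50.3 = 49.7 % and 100 − 53.7 = 46.3 %.

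**Assumptions.** Hazards are constant and independent. The cited control figures are read as Kaplan-Meier values. The whole death hazard is taken to compete with failure. The last is an upper-end choice, because some deaths follow a local failure.

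**Formulas**, with f the failure hazard and d the death hazard per year:
- f = −ln(local control)/2 and d = −ln(survival)/2
- 1-KM at t = 1 − exp(−f t)
- Cumulative incidence at t = f/(f + d) × [1 − exp(−(f + d) t)]

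**Single fraction, 2 years.** f = −ln(0.786)/2 = 0.1204; d = −ln(0.503)/2 = 0.3436.
- 1-KM = 1 − 0.786 = 0.214, which returns the cited control figure.
- Cumulative incidence = 0.1204/0.4640 × (1 − 0.786 × 0.503) = 0.2595 × 0.6046 = 0.157.

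**Multi-fraction, 2 years.** f = −ln(0.779)/2 = 0.1249; d = −ln(0.537)/2 = 0.3109.
- 1-KM = 0.221.
- Cumulative incidence = 0.1249/0.4358 × (1 − 0.779 × 0.537) = 0.2866 × 0.5817 = 0.167.

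**2-year results over the cited ranges**

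| Local control / survival at 2 years | 1-KM | Cumulative incidence | Excess (points) | Ratio |
|---|---|---|---|---|
| Single, 78.6 % / 50.3 % | 21.4 % | 15.7 % | 5.7 | 1.36 |
| Multi, 77.9 % / 53.7 % | 22.1 % | 16.7 % | 5.4 | 1.33 |
| 90 % / 50.3 % | 10.0 % | 7.3 % | 2.7 | 1.37 |
| 90 % / 53.7 % | 10.0 % | 7.5 % | 2.5 | 1.34 |
| Single, 78.6 % / 73 % | 21.4 % | 18.5 % | 2.9 | 1.16 |
| Single, 78.6 % / 33 % | 21.4 % | 13.2 % | 8.2 | 1.62 |
| Multi, 77.9 % / 89 % | 22.1 % | 20.9 % | 1.2 | 1.06 |
| Multi, 77.9 % / 33 % | 22.1 % | 13.7 % | 8.4 | 1.62 |

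**Effect on the contrast between arms.** On the matched figures the arms differ by 22.1 − 21.4 = 0.7 points on 1-KM and 16.7 − 15.7 = 1.0 point on cumulative incidence. The contrast hardly moves; the level does.

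**Distant failure.** The article gives no rate. Purely as an assumption, take a 2-year 1-KM of 30 to 70 % and let 10 to 100 % of the death hazard fall on patients without distant failure. The ratio of 1-KM to cumulative incidence then runs from about 1.03 to 1.36. It is smallest when most deaths follow distant failure.

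**The case against.** **Censoring of deaths is inferred.** The article does not define events or censoring for the failure endpoints, and a full protocol or analysis plan may do so. If death were counted as an event, the point would fall. This stands as a caveat. But the article lists the failure endpoints apart from disease free survival and names no death component, so censoring is the natural reading.

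**Kaplan-Meier answers a different question.** For local efficacy, with survival judged separately, failure net of death is a defensible quantity, and 1-KM is not wrong as an estimate of it under independence. This stands too. The error lies in reading the curve as the proportion of patients who fail, and nothing in the article guards against that.

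**The wrong arm might be selected.** A reader might infer this because local failure enters the first selection step. The documents do not support it. That step pairs local failure with overall survival and turns on whether outcomes differ significantly. The stated log-rank test is a valid comparison of cause-specific hazards and would be unchanged by the fix.

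**A mortality difference between arms might distort the Kaplan-Meier curves.** Under the assumptions used here it would not: 1 − exp(−f t) contains no death hazard. It is the cumulative incidence that falls as deaths rise, so an arm with more deaths would show fewer local failures. That is a reason to read it beside overall survival.

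**The size is uncertain.** The survival figures come from a review, not from a trial assumption, and at 89 % survival the excess is about 1 point. With 90 % control the excess of 2.5 to 2.7 points is well inside sampling error: 1.96 × √(0.10 × 0.90/42) = 0.091, about 9 points either way. This limits the practical weight. But the excess always runs in one direction, and the confidence interval does not reflect it.

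**Conclusion.** The point holds in a limited form. Applied as written to time to local failure and time to distant failure, the Kaplan-Meier rule gives 1-KM values above the proportion of patients who fail, with intervals centred on those values. For local failure at 2 years the excess is about 5 to 6 points on the matched Background figures (roughly a third in relative terms), 2.5 to 2.7 points if control is near 90 %, and about 1 to 8 points over the cited survival ranges. This rests on constant, independent hazards, on reading the cited control rates as Kaplan-Meier values, and on the whole death hazard competing with failure.

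A reader might extend the calculation to 5 years, where it gives 45.2 % against 23.4 % (single fraction) and 46.4 % against 25.4 % (multi-fraction). Those values extrapolate constant hazards well past the cited data. For single fraction they imply 5-year survival of exp(−5 × 0.3436) = 18 %, whereas the Discussion cites 36 % after resection of lung metastases, albeit in a different population. They show the direction of drift, not a size to rely on. The excess for distant failure is unknown.

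The primary toxicity endpoint, the sample size, overall survival, disease free survival and the log-rank comparison are unaffected.

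**What to change.** In the Statistical analysis section, separate the endpoints:
- For time to local failure and time to distant failure, report cumulative incidence (Aalen-Johansen) per arm with 95 % confidence intervals, with death without that failure as the competing event. State this event definition explicitly.
- Keep the log-rank test for these endpoints and label it a comparison of cause-specific hazards.
- Keep Kaplan-Meier for overall survival and disease free survival.

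The cost is a few lines of wording and a standard procedure. No extra patients or data are needed: deaths are already collected for overall survival, and the same approach is planned for the toxicity sensitivity analysis, which "will estimate the toxicities using cumulative incidences with death as a competing event".

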### Health economics: assessment of quality of life

For the purposes of the economic evaluation, HRQOL will be assessed using the EQ5D-5 L, a validated self-completed multi-attribute utility measure which will be used to estimate Quality adjusted life years (QALYs) for use the economic evaluation [15, 16]. This 5 item scale covers the following dimensions: mobility, self-care, usual activities, pain/discomfort and anxiety/depression, with each dimension having five levels. Participants will complete both measures at baseline and during follow-up.

### Health economics: assessment of resource use and costs

The direct resources associated with the delivery of SABR will be measured by observing the health care professional time and consumables required to plan and deliver of the radiotherapy intervention; an average cost/fraction will be calculated, reflecting Australian equipment and practice. Patient costs will be measured in terms of travel time and clinic time (i.e. time away from usual activities). Any visits to Emergency Departments or admissions to hospital will be captured directly from hospital records. Consent will be obtained from participants to access their Medicare Benefits Scheme (MBS) and Pharmaceutical Benefits Scheme (PBS) claims through Medicare (or appropriate national health administration) in order to capture any ancillary health expenses not costed directly to the primary cancer hospital provider. Hospital-specific costs and market prices are likely to be available for most of the resource items (e.g. MBS-fees). In the absence of market prices, data from the literature and expert opinion will be used to estimate unit prices. Results will be presented as total health care (by type) used, cost per unit of health care (e.g. PBS price) and total cost of health care used over the period of the trial and follow-up (3-years).

### Health economics analysis

The results of the economic evaluation will be reported as net costs and benefits for ARM 1 versus ARM 2. The costs of each ARM will take into account any cost-savings due to avoided health care utilisation and/or toxicities. Mean estimates of costs will be used and confidence intervals will be generated by boot-strapping the data. Benefits will be measured via the EQ5D5L questionnaire. Results will be presented in terms of the incremental cost-effectiveness ratio (ICER) as a cost/QALY gained. The incremental QALY will represent the improvement in quality of life between ARM 1 and ARM 2. The robustness and validity of the cost-effectiveness analysis will be explored using probabilistic sensitivity analysis.

### Sample size calculation

The maximum acceptable toxicity rate (grade 3 or higher adverse events) is considered to be 5 %. The desired upper limit of the 80 % confidence interval for a true toxicity rate of 5 % is 17 %. For a one-sided exact test for proportion with alpha = 0.1 and 80 % power, the required sample size is 38 evaluable patients for each arm of the trial. Assuming that up to 8 % of participants may be considered ineligible/unanalysable, 42 participants will be recruited in each arm.

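### The 8 % loss allowance does not fit a primary toxicity analysis limited to one-year completers: at the survival quoted in the Background, about 30-31 of 42 per arm would be evaluable, not 38

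*Protocol article*

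**What the plan says.** The Sample size calculation section sets the limit: "The maximum acceptable toxicity rate (grade 3 or higher adverse events) is considered to be 5" %. It adds a precision target: "The desired upper limit of the 80 % confidence interval for a true toxicity rate of 5 % is 17" %. The test behind the design is an exact one for a single proportion, one-sided at alpha 0.1 with power of 80 %. From this the section concludes: "the required sample size is 38 evaluable patients for each arm of the trial". The recruited number follows: "Assuming that up to 8 % of participants may be considered ineligible/unanalysable, 42 participants will be recruited in each arm".

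The Statistical analysis section defines who enters the primary analysis: "The first method (primary analysis) will evaluate the toxicities for participants who complete 1 year of follow up". Death is handled, as a competing event, only in the second method, which is labelled a sensitivity analysis.

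The Background gives the only survival figures for SABR to lung metastases. For the single-fraction series, weighted 2-year overall survival is 50.3 % (range 33-73 %). For the fractionated series: "The corresponding 2-year weighted overall survival was 53.7" % (range 33-89 %). The article gives no 1-year survival and no separate allowance for death.

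**The concern.** On the wording of the primary analysis, a patient who dies within the year is not evaluable. Reaching 38 of 42 tolerates four losses per arm from all causes together (4/42 = 9.5 %). The survival in the Background implies that 46-50 % of patients die within two years. Both can hold only if few of those deaths fall in the first year.

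Three things are at stake. The stated evaluable number would not be reached. The precision target, a 17 % upper limit, becomes harder to meet. And the completer rule removes a patient who has grade 3-4 toxicity and then dies before 12 months, although the primary endpoint counts toxicity within 12 months of finishing treatment. This endpoint also decides whether an arm can be considered for the phase III trial.

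**Working it through.** **Inputs.** Maximum acceptable rate 5 %, 17 % upper limit, alpha 0.1 one-sided exact, 80 % power, 38 evaluable, 8 % allowance and 42 recruited per arm (Sample size calculation); completers only (Statistical analysis); 2-year survival 50.3 % and 53.7 %, ranges 33-73 % and 33-89 % (Background); 35-month median survival in a surgical registry (Discussion). The article names no alternative rate for the test. I take 17 %, the only other rate given.

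**1. The plan's own figures.** With n = 38, 5 % against 17 % and alpha at most 0.1, the exact test rejects at 5 or more events (actual alpha 4.0 %) and has 79.75 % power. The inflation is 38/0.92 = 41.3, rounded up to 42. Both figures reproduce.

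**2. A check without a survival model.** Keeping 38 of 42 with no other loss requires that at most (4/42)/(1 - 0.503) = 19 % (single fraction) or (4/42)/(1 - 0.537) = 21 % (fractionated) of the two-year deaths occur in year 1.

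**3. Completers under a constant hazard.** One-year survival is the square root of two-year survival.

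- Single fraction: sqrt(0.503) = 0.709, so 29.1 % die in year 1; 42 x 0.709 = 29.8
- Fractionated: sqrt(0.537) = 0.733, so 26.7 % die in year 1; 42 x 0.733 = 30.8
- If the 8 % is lost in addition: 29.8 x 0.92 = 27.4 and 30.8 x 0.92 = 28.3
- Binomial chance of at least 38 completers of 42, deaths alone: 0.2 % and 0.6 %

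**4. Other survival assumptions, deaths alone.**

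- 2-year survival 33 %: 42 x 0.574 = 24
- 73 %: 42 x 0.854 = 36
- 89 %: 42 x 0.943 = 39.6, about 40 (36 with the 8 % as well)
- Straight-line survival to the central two-year figures: 42 x 0.752 = 31.6 and 42 x 0.769 = 32.3
- 35-month median: 0.5^(12/35) = 0.788, giving 33

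**5. Consequences.** Power is exact for 5 % against 17 %, with the cut-off re-derived at each n. The upper limit is that of the exact (Clopper-Pearson) two-sided 80 % interval.

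| Evaluable | Reject at | Power | Most events with upper limit < 17 % | Chance of that at a true rate of 5 % |
|---|---|---|---|---|
| 24 | 4 | 60.1 % | 1 | 66.1 % |
| 27 | 4 | 69.7 % | 1 | 60.6 % |
| 28 | 4 | 72.5 % | 1 | 58.8 % |
| 30 | 4 | 77.5 % | 2 | 81.2 % |
| 31 | 4 | 79.7 % | 2 | 79.9 % |
| 33 | 4 | 83.6 % | 2 | 77.3 % |
| 36 | 5 | 75.6 % | 2 | 73.2 % |
| 38 | 5 | 79.75 % | 3 | 88.0 % |
| 40 | 5 | 83.3 % | 3 | 86.2 % |

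Both measures are saw-toothed because events are whole numbers. Power at n = 32-35 is 82-87 %, higher than at 38. For the upper limit, by contrast, every size from 22 to 37 falls short of the 88 % at n = 38; the best is 81.2 %.

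**The case against.** Several objections stand in whole or in part.

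- **The allowance may already include deaths.** A patient outside the primary analysis is unanalysable, so the 8 % can be read as the total loss. Taking deaths and then a further 8 % is one reading only. The central figure is therefore 30-31, with 27-28 as the case where losses stack.
- **Power.** A reader might infer that the trial loses its stated 80 % power. The article's figures do not show that: at 30-31 evaluable the loss is 0-2 points. A loss of 7-10 points needs the stacked losses. A larger one would need the cut-off of 5 events to be kept with fewer patients, and the article fixes no cut-off.
- **Survival.** The 27-29 % is an extrapolation from two-year means in a pooled review, not a documented figure. The trial also selects fit patients (ECOG 0-1, at most three metastases, controlled primary and extrathoracic disease). At the best quoted survival, 89 %, about 40 remain from deaths alone and the plan's 38 holds.
- **Arithmetic.** A reader might call 42 a calculation error. It is not: 38 and 42 both reproduce. The fault is that the allowance does not match the analysis set.
- **Partly handled.** A competing-risk analysis is already planned, but only as a sensitivity analysis.

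The mismatch remains. Even if the 8 % is read as covering deaths, it is too small at the central survival figures, under a constant hazard, a straight line or the surgical median. Nor is it a detail left to a document not shown: the article itself fixes the primary analysis set, the allowance and the recruited number.

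**Conclusion.** The concern holds. At the survival quoted in the Background, 42 per arm should give about 30-31 one-year completers from deaths alone, against the 38 stated, with a range of 24 to 40 over the quoted 33-89 %. Only the 89 % extreme keeps 38, and then with almost no other loss. The chance of an upper limit below 17 % at a true rate of 5 % falls from 88 % to about 80-81 %, or 59-61 % if the 8 % is lost as well. The loss of power is small at 30-31 and is not the main point. The exclusion of patients who have toxicity and then die within the year follows from the wording whatever the survival.

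The numbers rest on three assumptions: a constant hazard, pooled series that may do worse than the trial population, and 17 % as the alternative rate. The shortfall in evaluable patients is robust to the shape of the survival curves tried; the exact power is not.

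**What to change.** Make the primary analysis include all eligible treated patients, count any qualifying toxicity before death, and treat toxicity-free death within 12 months as a competing event. This promotes the method now planned as the sensitivity analysis. The 8 % allowance then needs to cover only ineligible patients and living dropouts, and 42 per arm remains consistent with 38 evaluable if those losses stay within it.

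The cost is a change of wording and no added patients. There is a small downside: early toxicity-free deaths stay in the denominator as non-events, so the estimand changes slightly and the rate is lower than among survivors. The binomial calculation carries over directly only where no living patient is censored before 12 months, so the 80 % interval for the cumulative incidence should be specified.

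If completers stay primary, restate the expected evaluable number as about 27-31 per arm, state the survival assumption behind it, and give the matching power (about 70-80 %) and chance of meeting the 17 % upper limit (about 59-81 %). That also needs no added patients, but the stated properties become less favourable and patients with toxicity who die early are still dropped.
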